# Data Collection and Follow-up

Data will be collected in the REDCap database set up at National Taiwan University Hospital. The following variables will be gathered from the rescue reporting form: patient demographics (age and sex), pre-existing comorbidities (hypertension, diabetes mellitus, COPD, asthma, liver disease, kidney disease, heart disease, seizure, psychotic disorder, and cancer), arrest characteristics (witnessed arrest and bystander CPR), arrest location (household, workplace, public space, and nursing home), and EMT-performed procedures (oral/nasal airway, SGA, ETT, mechanical CPR, AED, defibrillation, IO/IV catheter, epinephrine injection, and normal saline infusion). Prehospital ROSC will also be reported on the form. These data will be collected on a weekly basis.

Other prognostic outcomes (any ROSC, 24-hour survival, survival to discharge, and neurological function at discharge) will be collected from the reports of the hospitals to which the patients are sent. Follow-up frequency for these outcomes will be one month.

Ventilation and chest compression feedback data will be exported from the Zoll X-series in .csv format. These files will be uploaded to the REDCap database on a weekly basis.

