# Analytic Plan

Statistical Package for the Social Sciences (version 26.0; IBM Corp., Armonk, NY, USA) will be used for the statistical analyses in this study. Intention to treat analysis will be adopted for comparing outcomes between interventions. Firstly, descriptive statistics of demographics (Table 1), ventilation parameters (Table 2), and outcomes (Table 3) among APV group and BVM group will be presented as number (percentage) for categorical variables and median (interquartile range) for continuous variables. Categorical variables will be compared using Pearson’s chi-square test or Fisher’s exact test, while continuous variables will be compared using Mann–Whitney U test. Secondly, multivariable logistic regression will be conducted to investigate the association of different ventilation interventions and patients’ outcomes, adjusting for potential confounders. Subgroup analysis, presented as a forest plot, will also be performed to investigate the impact of different interventions on outcomes in different subgroups. We will also compare the adjusted absolute difference between ventilation parameters measured in the APV and BVM group using the linear mixed-effects model (LMM). For the LMM, variables including demographics, prehospital information, resuscitation managements were included as fixed effects, whereas each patient will be modeled as a random effect. Two tail p-values <0.05 will be considered as statistically significant and will be corrected with Bonferroni correction in post-hoc analyses.

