# Dummy Tables

| Table 1. Baseline characteristics | | |
| --- | --- | --- |
|  | APV | BVM |
|  | (n=XXX) | (n=XXX) |
| Age, years (mean ± SD) | XX ± XX | XX ± XX |
| Males, n (%) | XX (XX.X%) | XX (XX.X%) |
| Pre-existing comorbidity |  |  |
| Diabetic mellitus, n (%) | XX (XX.X%) | XX (XX.X%) |
| Hypertension, n (%) | XX (XX.X%) | XX (XX.X%) |
| Cancer, n (%) | XX (XX.X%) | XX (XX.X%) |
| COPD, n (%) | XX (XX.X%) | XX (XX.X%) |
| Asthma, n (%) | XX (XX.X%) | XX (XX.X%) |
| Stroke, n (%) | XX (XX.X%) | XX (XX.X%) |
| Liver disease, n (%) | XX (XX.X%) | XX (XX.X%) |
| Kidney disease, n (%) | XX (XX.X%) | XX (XX.X%) |
| Heart disease, n (%) | XX (XX.X%) | XX (XX.X%) |
| Seizure, n (%) | XX (XX.X%) | XX (XX.X%) |
| Psychotic disorder, n (%) | XX (XX.X%) | XX (XX.X%) |
| Witnessed arrest, n (%) | XX (XX.X%) | XX (XX.X%) |
| Bystander CPR, n (%) | XX (XX.X%) | XX (XX.X%) |
| Arrest location |  |  |
| Household, n (%) | XX (XX.X%) | XX (XX.X%) |
| Working place, n (%) | XX (XX.X%) | XX (XX.X%) |
| Public space, n (%) | XX (XX.X%) | XX (XX.X%) |
| Nursing home, n (%) | XX (XX.X%) | XX (XX.X%) |
| Others, n (%) | XX (XX.X%) | XX (XX.X%) |
| Oral airway, n (%) | XX (XX.X%) | XX (XX.X%) |
| Nasal airway, n (%) | XX (XX.X%) | XX (XX.X%) |
| SGA, n (%) | XX (XX.X%) | XX (XX.X%) |
| ETT, n (%) | XX (XX.X%) | XX (XX.X%) |
| Mechanical CPR, n (%) | XX (XX.X%) | XX (XX.X%) |
| AED, n (%) | XX (XX.X%) | XX (XX.X%) |
| Defibrillation, n (%) | XX (XX.X%) | XX (XX.X%) |
| IO, n (%) | XX (XX.X%) | XX (XX.X%) |
| IV, n (%) | XX (XX.X%) | XX (XX.X%) |
| Epinephrine, n (%) | XX (XX.X%) | XX (XX.X%) |
| Normal saline, n (%) | XX (XX.X%) | XX (XX.X%) |

| Table 2. Ventilation parameters between patients in APV and BVM group | | |
| --- | --- | --- |
|  | APV | BVM |
|  | (n=XXX) | (n=XXX) |
| Ventilation rate, bpm (median ± IQR) | XX ± XX | XX ± XX |
| Tidal volume, mL (median ± IQR) | XX ± XX | XX ± XX |
| EtCO2, mmHg (median ± IQR) | XX ± XX | XX ± XX |

| Table 3. Outcome comparison between patients in APV and BVM group | | |
| --- | --- | --- |
|  | APV | BVM |
|  | (n=XXX) | (n=XXX) |
| Prehospital ROSC, n (%) | XX (XX.X%) | XX (XX.X%) |
| Any ROSC, n (%) | XX (XX.X%) | XX (XX.X%) |
| 24-hour survival, n (%) | XX (XX.X%) | XX (XX.X%) |
| Survival to hospital discharge, n (%) | XX (XX.X%) | XX (XX.X%) |
| Good neurological function after discharge, n (%) | XX (XX.X%) | XX (XX.X%) |

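### Neither the variable list nor Table 1 names first monitored rhythm or a response interval, and Table 1 presents post-allocation crew procedures as baseline characteristics

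*Protocol*

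**What the plan says.** Data Collection and Follow-up introduces its list with "The following variables will be gathered from the rescue reporting form". The list covers age, sex, comorbidities, "arrest characteristics (witnessed arrest and bystander CPR"), arrest location, and "EMT-performed procedures (oral/nasal airway, SGA, ETT, mechanical CPR, AED, defibrillation, IO/IV catheter, epinephrine injection, and normal saline infusion"). The monitor contributes a separate file: "Ventilation and chest compression feedback data will be exported from the Zoll X-series in .csv format". No heart rhythm and no time interval is named in either source.

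Table 1 in Dummy Tables is titled as baseline characteristics. Its rows follow the list closely: they include "Bystander CPR, n" and "Defibrillation, n", along with AED, IO, IV and epinephrine, but no rhythm row and no response-time row. Outcome measurement, however, lists IV catheter insertion and epinephrine injection among the secondary outcomes.

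For the patient outcomes, Analytic Plan states that "multivariable logistic regression will be conducted to investigate the association of different ventilation interventions and patients’ outcomes, adjusting for potential confounders". It does not name the covariates.

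**The concern.** First monitored rhythm and the call-to-arrival interval are both settled before the ventilation device is connected, so the arm cannot change them. That makes them suitable for judging whether the groups are comparable and for adjusting the ROSC analysis. An analysis plan written later can choose among recorded variables, but it cannot tabulate or adjust for something that was never recorded. This is why the data list belongs in the protocol.

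Defibrillation and AED use are different in kind. They are the only rhythm-related items listed, but they are actions taken by an unblinded crew that already knows its arm. Backgrounds argues that the device may free crew members for other tasks, so procedures may themselves respond to the arm. Placing them under a baseline title invites a reader, or a later analyst, to treat them as pre-treatment covariates.

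Two features of the design raise the value of a true baseline factor. Allocation is by two-week period and is announced before the period starts (Randomization and blinding; Study procedures and workflow). And Exclusion criteria removes patients in whom no advanced airway is ever placed, which is determined after the arm is known. If that exclusion worked differently in the two arms, the rhythm mix of those analysed could differ, and rhythm would be the natural variable to show it.

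**Working it through.** **Text check.**

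| Item | Data list | Table 1 | Secondary outcome |
|---|---|---|---|
| First monitored rhythm | no | no | no |
| Response interval | no | no | no |
| AED, defibrillation | yes, as crew procedures | yes, as baseline | no |
| IV, epinephrine | yes, as crew procedures | yes, as baseline | yes |
| Stroke | no | yes | no |

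The first two rows establish the omission. The fourth is an inconsistency within the protocol: the same items are baseline in one place and outcomes in another. The last shows that the data list is not exhaustive.

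**Plan's own figure.** Sample Size Estimation uses 0.567 against 0.433, two-sided alpha 0.05, power 0.80 and 1:1 allocation. With the pooled-variance formula:

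n per arm = [1.960 × √(2 × 0.5 × 0.5) + 0.8416 × √(0.567 × 0.433 + 0.433 × 0.567)]² / 0.134² = (1.386 + 0.590)² / 0.01796 ≈ 217.4, so 218 per arm and 436 in total.

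436 × 1.12 = 488.3, and 488 / 0.95 = 513.7, so 514. The stated figures reproduce, and this point does not change them. After the design effect the plan is worth 436 independent patients, which is used below.

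**Size of the loss for rhythm.** The protocol gives neither the shockable share q nor the odds ratio linking rhythm to ROSC, so both are assumed. The marginal ROSC rates are held at 0.433 and 0.567.

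Unadjusted: log odds ratio = 2 × ln(0.567/0.433) = 0.539; SE = √(2 / (218 × 0.2455)) = 0.193; power = Φ(0.539/0.193 − 1.96) ≈ 0.797.

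Adjusted, worked for q = 0.20 and odds ratio 6:
- The marginal rates require control-arm ROSC of 0.350 (non-shockable) and 0.764 (shockable), and APV-arm ROSC of 0.495 and 0.855. The conditional treatment odds ratio is 1.819 (log 0.598).
- Information weights n·q·p(1−p) are 39.7 and 43.6 in the non-shockable stratum, and 7.86 and 5.41 in the shockable one.
- Treatment information = 39.7 × 43.6 / 83.3 + 7.86 × 5.41 / 13.27 ≈ 24.0, so SE ≈ 0.204.
- Power = Φ(0.598/0.204 − 1.96) ≈ 0.834.

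The SD of chance imbalance in rhythm is √(2q(1−q)/218). Multiplying it by the control-arm ROSC difference between rhythm strata gives the shift in the ROSC difference for a one-SD imbalance. In the worked case this is 0.0383 × (0.764 − 0.350) ≈ 0.016.

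| q | Rhythm OR | Adjusted power (unadjusted 0.797) | Imbalance SD, points | Shift in ROSC difference, points |
|---|---|---|---|---|
| 10% | 2 | 0.800 | 2.9 | 0.5 |
| 10% | 4 | 0.810 | 2.9 | 0.9 |
| 10% | 6 | 0.816 | 2.9 | 1.2 |
| 20% | 2 | 0.803 | 3.8 | 0.7 |
| 20% | 4 | 0.821 | 3.8 | 1.3 |
| 20% | 6 | 0.834 | 3.8 | 1.6 |
| 30% | 2 | 0.806 | 4.4 | 0.8 |
| 30% | 4 | 0.830 | 4.4 | 1.5 |
| 30% | 6 | 0.849 | 4.4 | 1.8 |

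A simulation (N = 436, 1,500 runs per scenario) agrees. Unadjusted against adjusted power was 0.807 vs 0.815 (10%, OR 3), 0.801 vs 0.817 (10%, OR 6), 0.805 vs 0.823 (20%, OR 3) and 0.805 vs 0.842 (20%, OR 6): gains of 0.8, 1.6, 1.8 and 3.7 points. The simulation error of each power is about √(0.8 × 0.2 / 1500) = 1 point.

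No comparable calculation was made for the response interval.

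**The case against.** The strongest reply is that the protocol never calls its list complete. Stroke appears in Table 1 but not in the list, Data Management refers to checks on date fields that the list does not mention, and the rescue form is not shown. A reader might infer that rhythm is not being recorded at all. The text supports only that the protocol names it nowhere, and so nothing commits the trial to recording or using it. This part of the reply stands and limits the wording.

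A reader might also infer that the ROSC model will adjust for defibrillation in place of rhythm. The documents do not say so. Covariates for that model are unnamed, and naming them is commonly left to an analysis plan. The phrase "variables including demographics, prehospital information, resuscitation managements were included as fixed effects" belongs to the mixed model for ventilation parameters, not to ROSC. Adjustment for defibrillation is a possibility that the protocol leaves open, not a stated plan.

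It is also fair that the gain is small, that defibrillation by arm gives an imperfect indirect view of rhythm balance, that the response interval is unquantified, and that the prognostic weight of both factors is assumed from general clinical knowledge. None of this answers the labelling problem, which rests on the protocol alone.

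**Conclusion.** The point holds as an omission and a mislabelling. First monitored rhythm and response interval are missing from both the data list and Table 1, and Table 1 presents post-allocation procedures as baseline, two of which the protocol elsewhere treats as outcomes.

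It would be wrong to conclude that the primary comparison is invalid: leaving out a prognostic factor does not by itself bias the unadjusted randomised comparison. The loss is modest. It is about 1 to 4 points of power for a shockable share of 10-20% and an odds ratio of 3-6; over the wider grid (10-30%, 2-6) adjusted power is 0.80 to 0.85 against 0.80. A one-SD chance imbalance would move the ROSC difference by 0.5 to 1.8 points, against the planned 13.4. These figures treat 436 as the independent sample size and cover chance imbalance only. Any imbalance from exclusions made after allocation would come on top and cannot be sized from the protocol. The case for the response interval is qualitative.

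**What to change.** - Add first monitored rhythm (shockable or not) to Data Collection and Follow-up and to Table 1. Add the call-to-arrival interval where dispatch times are available, with a coding rule for patients who arrest during transport, whom the protocol also enrols.
- Look both up from existing case records for patients already enrolled, as far as possible, and report how many values are missing.
- Prespecify rhythm as a covariate in the logistic model for any ROSC.
- State that crew procedures performed after allocation (AED, defibrillation, IV or IO access, epinephrine and the like) will not be covariates in that model.
- Move those rows out of the baseline table into a table of care delivered, so that IV insertion and epinephrine appear once, as outcomes.

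The cost is two database fields, re-linkage for enrolled patients (Data Management keeps identifiers in a separate file) with some values missing, access to dispatch times that the protocol does not describe, and an amendment needing ethics approval. No extra patients and no change to treatment are needed.

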# Data Management

Data collected during the study will be entered into a secure, password-protected electronic database. The following procedures will be implemented to ensure data quality, confidentiality, and integrity:

1. **Data Entry and Coding**: Data will be double-entered by two independent data entry personnel to minimize data entry errors. Each data entry will then be cross-checked for discrepancies, which will be resolved by the direction of the trial. All data will be anonymized and coded prior to entry, with identifiers kept in a separate, secure file to maintain participant confidentiality.
2. **Data Quality Assurance**: Range checks will be implemented for numerical data fields to identify out-of-range or erroneous values. Additionally, logical checks (e.g., comparing date fields for chronological consistency) will be performed. Any identified data inconsistencies will be flagged for review, and corrections will be documented in an audit trail of the REDCap database.
3. **Data Security**: The database will be hosted on a secure server with restricted access provided by REDCap, limited to authorized study personnel.
4. **Data Storage**: All data will be stored in compliance with relevant regulations and institutional guidelines of National Taiwan University Hospital and Hsin-Chu County Fire Department. Upon study completion, data will be archived securely for a period of five years, in line with institutional and regulatory requirements. After this retention period, data will be anonymized and securely disposed of as per institutional policies.

# Analytic Plan

Statistical Package for the Social Sciences (version 26.0; IBM Corp., Armonk, NY, USA) will be used for the statistical analyses in this study. Intention to treat analysis will be adopted for comparing outcomes between interventions. Firstly, descriptive statistics of demographics (Table 1), ventilation parameters (Table 2), and outcomes (Table 3) among APV group and BVM group will be presented as number (percentage) for categorical variables and median (interquartile range) for continuous variables. Categorical variables will be compared using Pearson’s chi-square test or Fisher’s exact test, while continuous variables will be compared using Mann–Whitney U test. Secondly, multivariable logistic regression will be conducted to investigate the association of different ventilation interventions and patients’ outcomes, adjusting for potential confounders. Subgroup analysis, presented as a forest plot, will also be performed to investigate the impact of different interventions on outcomes in different subgroups. We will also compare the adjusted absolute difference between ventilation parameters measured in the APV and BVM group using the linear mixed-effects model (LMM). For the LMM, variables including demographics, prehospital information, resuscitation managements were included as fixed effects, whereas each patient will be modeled as a random effect. Two tail p-values <0.05 will be considered as statistically significant and will be corrected with Bonferroni correction in post-hoc analyses.

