# Trial Design

This trial is a pragmatic, open-label, multi-center cluster randomized controlled trial.

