## Randomization and blinding

The participating EMS teams will be divided into two randomized clusters. Each cluster will be assigned to either the APV or BVM group. The duration of a cluster is 14 days (two weeks). The study center will instruct the clusters to alternate between APV and BVM according to a sequence determined by random allocation.

The randomization process was done by a research assistant. The sequence was generated using tool by Sealed Envelope Ltd. 2022 [20]. The formula this program used is based on the textbook *Clinical Trials: A Practical Approach* [21]. In the program, the seed is generated by a random table by Microsoft Excel. Each block contains 6 clusters. However, the EMTs are not aware of the randomization and allocation method.

The allocation sequence will be revealed until three days before the next cluster begins via social network application.

Blinding of the EMTs or hospital staff is not feasible because the ventilation equipment used in the study cannot be blinded

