# Sample Size Estimation

In the original version of sample size calculation, we chose a secondary outcome (ventilation rate) to be the reference to calculate the sample size. Because we couldn’t find any studies with a similar trial design and primary outcome as our study. The original sample size was 260 patients. However, in August 2024, we identified some comparable studies to guide our calculations more precisely.

We chose the pilot study by Shin et al., which compared automatic mechanical ventilation (MV) with manual bag ventilation (BV) during CPR [19]. In that study, the primary outcome, any ROSC, was achieved in 56.7% of the MV group and 43.3% of the BV group—values closely aligning with our expected ROSC rates. Thus, we conducted an initial power analysis in G*Power 3.1 using the following parameters: Z test family, difference between two independent proportions, two-tailed test, proportions of 0.567 and 0.433, alpha of 0.05, power of 0.8, and equal allocation (1:1). This analysis suggested 218 patients per arm, totaling 436.

To account for the clustering effect due to randomization at the EMS team level, we included an intraclass correlation coefficient (ICC). Our EMS teams are expected to recruit 3 patients per cluster (over 14 days). Given the substantial variability in OHCA patient conditions, we assumed a low ICC of 0.06. The design effect was therefore calculated as 1+(3−1) ×0.06=1.12, adjusting our sample size to 488. Finally, with an estimated 5% dropout rate, the final required sample size was increased to 514 patients.

Figure 3. Sample size calculation by G*Power 3.1

[figure not shown]

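### Allocation and sample size are by 14-day EMS cluster, but the planned tests and models have no term for that cluster

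*Protocol*

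**What the plan says.** Under Trial Design: "This trial is a pragmatic, open-label, multi-center cluster randomized controlled trial". Under Randomization and blinding, "The duration of a cluster is 14 days (two weeks"), and "The study center will instruct the clusters to alternate between APV and BVM according to a sequence determined by random allocation". Allocation is in blocks of 6 clusters.

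Under Sample Size Estimation: "To account for the clustering effect due to randomization at the EMS team level, we included an intraclass correlation coefficient (ICC"). The inputs are an ICC of 0.06 and 3 patients per cluster. The resulting design effect of 1.12 takes the total from 436 to 488, and 5% dropout takes it to 514.

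Under Analytic Plan: "Categorical variables will be compared using Pearson’s chi-square test or Fisher’s exact test". Continuous variables get a Mann–Whitney U test. Outcomes are then modelled by multivariable logistic regression adjusted for unspecified confounders. Ventilation parameters get a linear mixed model with covariates as fixed effects, "whereas each patient will be modeled as a random effect". The section mentions no cluster random effect, GEE, robust standard error or cluster-level analysis.

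Under Interim analysis and stopping criteria, the ROSC comparison is a chi-square test on a 2x2 table at p < 0.05.

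**The concern.** The protocol assumes that patients in the same cluster are correlated when it sets the sample size, and assumes that they are independent when it sets the tests. The patient random effect in the mixed model does not bridge this gap. It handles repeated readings within one patient, not similarity between patients treated under the same allocation.

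This is not a detail left for a later document, because the section names the tests, the models, the random effect and the significance threshold. If it is followed as written, the extra 52 patients (488 − 436) enrolled to pay for clustering are counted as independent information. P-values for any ROSC may then be too small and intervals too narrow. The same applies to the secondary outcomes and to an interim test on which the trial may be stopped.

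**Working it through.** **Inputs (Sample Size Estimation).** "two-tailed test, proportions of 0.567 and 0.433"; "alpha of 0.05, power of 0.8, and equal allocation (1:1"); ICC 0.06; m = 3 patients per cluster; 5% dropout.

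**Reproducing the plan's figures.**
- The two-proportion z-test with pooled variance gives 218 per arm, 436 in total.
- Design effect DE = 1 + (m − 1) × ICC = 1 + 2 × 0.06 = 1.12.
- 436 × 1.12 = 488.3, stated as 488.
- 488 / 0.95 = 513.7, so 514.

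All the stated figures reproduce.

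**Error of a test that ignores the cluster.** If the true variance is DE times the naive variance, the naive standard error is too small by √DE, and the actual two-sided error of a nominal 5% test is 2 × [1 − Φ(1.96 / √DE)].
- Equal clusters of 3: √1.12 = 1.058 and 1.96 / 1.058 = 1.852. The error is 6.4% and the coverage of a 95% interval is 93.6%. The naive interval is 1 − 1/1.058 = 5.5% too narrow.
- Poisson cluster sizes with mean 3 (assumed; squared coefficient of variation 1/3): DE = 1 + [(1/3 + 1) × 3 − 1] × 0.06 = 1.18 and 1.96 / √1.18 = 1.804. The error is 7.1%.
- A beta-binomial simulation with 164 clusters and 40,000 runs gives 6.5% with fixed sizes and 7.3% with Poisson sizes.

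**Sensitivity to the ICC (m = 3, equal clusters).**

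| ICC | DE | Type I error |
| --- | --- | --- |
| 0.01 | 1.02 | 5.2% |
| 0.03 | 1.06 | 5.7% |
| 0.06 | 1.12 | 6.4% |
| 0.10 | 1.20 | 7.4% |

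**Allowing for alternation.** The formula above treats the whole ICC as specific to the randomised cluster-period. Teams alternate between arms, so the part of the correlation that is stable within a team appears in both arms and largely drops out of the comparison. This was simulated with about 488 patients, Poisson cluster sizes of mean about 3, blocks of 6 within team, and 6 or 9 teams. The number of teams is an assumption; the protocol gives none.

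| How the ICC of 0.06 is divided | Type I error of the chi-square test |
| --- | --- |
| All stable within team | about 5% |
| Half team, half 14-day period | about 6–6.5% |
| All specific to the 14-day period | about 7.2–7.6% |

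**Power.** With 488 evaluable patients, a cluster-adjusted test has 80.1% power at the plan's rates. A calculation that ignores clustering shows 84.4%.

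**The case against.** The strongest reply is that the alternating design removes much of the problem. This stands in part. If the ICC reflects lasting differences between teams, the chi-square test holds close to 5%. The protocol ties its ICC to randomisation at EMS team level and does not say how much is specific to a 14-day period. It is therefore not certain that the standard errors are too small. But the protocol's own design effect treats the ICC as within-cluster, and it defines a cluster as 14 days. Its analysis should be consistent with that.

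A second reply is that the chi-square tests are introduced alongside descriptive statistics and that the regression comes afterwards. That is fair, but the regression is given no cluster term either.

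Several stronger readings are tempting and are not supported:
- *Much larger inflation for ventilation parameters because they depend on the crew.* A stable crew effect is the component that alternation cancels. In simulation, a wholly team-level ICC as high as 0.30 for a binary outcome still gave an error of 4.9–5.5%.
- *An error of 10% or more from larger clusters.* At ICC 0.06 this needs about 8 patients per cluster or more. The only cluster size the protocol states is 3.
- *Team and calendar effects left uncontrolled.* Allocation in blocks of 6 tends to balance the arms over time, alternation helps to balance teams, and the confounder list is not specified. The protocol does not establish this fault.
- *A change of wording alone is enough.* Data Collection and Follow-up lists neither EMS team nor 14-day period among the variables collected, so it cannot be assumed that both are in the dataset.

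**Conclusion.** The point holds as a mismatch between design and analysis, with a modest numerical effect. The trial randomises and is sized by 14-day cluster, and none of the tests or models it names, including the interim test, has a term for that cluster.

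At the plan's ICC of 0.06 and 3 patients per cluster, the nominal 5% test runs at about 6.4%, or about 7% with Poisson-varying cluster sizes. Allowing for alternation, the plausible range is about 5% to 7.5%. The position within it depends on the share of the ICC that is specific to the 14-day period, which the protocol does not give. The range also rests on the assumed ICC being correct and on an assumed number of teams.

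The inflation is small, but it bears on the primary outcome and on a test that can stop the trial. It is also avoidable, because the sample size already allows for clustering.

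**What to change.** - Name one primary analysis of any ROSC that accounts for the randomised cluster-period. Examples are mixed-effects logistic regression with a cluster-period random effect and a team effect, or GEE with cluster-robust standard errors.
- Label the chi-square and Fisher results as descriptive.
- In the linear mixed model, add the cluster-period effect above the patient effect.
- Replace the interim 2x2 chi-square with a cluster-adjusted test.
- State in Data Collection and Follow-up that EMS team and 14-day period are recorded for every case. For cases already enrolled, confirm that both can be recovered.

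**Cost.** The target of 514 stays, since it already includes the design effect. Confidence intervals become slightly wider: at DE 1.12, about 6% wider than the naive ones (factor 1.058). The remaining work is a protocol amendment and, if team and period are not already held, adding two variables to the dataset.
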